### Data collection and management

All data from the census, passive case detection and active case detection activities will be collected using electronic case record forms (eCRFs) using Open Data Kit (ODK [https://opendatakit.org]) and encrypted password protected Android devices. Completed eCRFs will be securely transferred to a 256-bit SSL encrypted and fire-walled ODK server, which is hosted at LSHTM [22]. We will design eCRFs in English and French languages to collect data on all aspects of the study, including, EPI vaccinations and SP distribution, longitudinal follow-up of children and all health facility visits. Automated programmes in R statistical software will push data to REDCap, software that is compliant with Good Clinical Practice for storing an audit trail of changes made during data cleaning, data management and further quality control checks [23]. Electronic data entry quality will be ensured by real-time error capture on ODK eCRFs, internal validation, consistency checks and stringent formatting constraints. The study protocol, standard operating procedures, data collection tools and other study documents will be freely available on request from coinvestigators and from the data repository website.

### Patient and public involvement and participant remuneration

The views of the relevant stakeholders were instrumental in developing the study protocol. Firstly, the intervention was designed during a co-creation workshop where stakeholders met to agree on the number, timing, and modality of SP doses as well as which areas would be included in the pilot implementation. Secondly, meetings with the clinical staff in the study areas as well as community leaders were held to provide input on the study procedures, including the eligibility criteria, piloting the questionnaire and other data collection mechanisms.

As is standard practice in both countries, study participants will not receive any financial renumeration for their participation. No payments for participants’ time or any costs associated with a routine health visit will be covered. As per the national strategy in both settings, all EPI, Vitamin A, and PMC services are free. For children participating in the active cohort all tests and any provided treatment will be provided at no cost to the participant.

### Dissemination of project findings

Dissemination of the study findings we will take multiple forms to maximise the reach of the information. Firstly, stakeholder meetings will take place within each study country where the interim and final results will be presented to inform programmatic decision-making on PMC implementation. Stakeholders will consist of the relevant NMP representative involved in policy as well as members of the community where the research took place so clinicians, CHWs, and the participants can see how their participation benefited research and translated into the results obtained. Peer-reviewed publications and presentations at national and international meetings will allow the results to be disseminated to the relevant scientific community. Authorship will follow the international committee of medical journal editors and equitable partnership guidelines. All papers will be submitted for publication in open access journals and anonymized data will be available for future research on institutional data repositories that can benefit the communities, where appropriate ethical approvals are in place.

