Each child in the active cohort will be followed-up for a maximum of seven visits at three-monthly intervals over 18 months, including the initial recruitment visit plus six subsequent follow-up visits (Fig. 4). During follow up visits at the household, verbal consent from the primary caregiver for continued participation of their child in the study will be recorded. A short questionnaire will be completed to collect data about any malaria or anaemia diagnosis or receipt of PMC since the last study visit, at which health facility care was sought and other relevant information. A blood sample will be collected following the same procedures outlined above.

Adverse events and safety of receiving PMC will be monitored by the MoH as part of the routine programmatic implementation of this intervention. Participant safety will be monitored throughout the study period and any adverse effects related to study procedures will be investigated using standardised procedures and managed according to national guidelines.

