### Data analysis

The primary analysis will be based on intention to treat (ITT), including all children residing in the intervention area as the exposed group. All available data up to the time of censuring (e.g., loss to follow-up, withdrawal, death, or study completion), irrespective of whether the child received any, part, or all the intended PMC doses. An additional per-protocol analysis will be completed which includes children who received at least one dose, all doses, or specific doses of PMC. The period of protection provided by SP is up to one-month post treatment and thus will constitute the protective window of those receiving the intervention. Data for both countries will be combined for analysis as well as assessed separately to ensure context specific nuances are fully assessed.

Incidence rates for malaria and anaemia will be calculated using multivariable Poisson regression, difference-in-difference, and interrupted time-series models comparing intervention and control areas [14–16]. Incidence rates, rate differences, and rate ratios between intervention and control area will be calculated for the ITT and per-protocol analysis. Malaria incidence will be determined by the number of malaria cases confirmed by either RDT or microscopy identified in either the passive or active cohort. Person-time at risk for each study outcome will be calculated based on the date of recruitment into the study population until the date of censuring or study end. For children who leave the study prior to the end date, the date of exit will be the date where they moved, withdrew from the study, or died. If that date is not known, the midpoint between the date of last contact and the date the loss was detected will be used. Protective effectiveness will be calculated for the intervention period including the 18 months of follow-up for the periods where PMC doses differ, stratified by first and second year of life, as well as during the post-intervention period, starting at 24 or 18 months of age in Cameroon and Côte d’Ivoire, respectively, to estimate any potential rebound in malaria.

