Where there are repeated measures per child, random effects or generalising estimating equations models will be used to adjust for non-independence of the data from the same individual. Regression models will assess factors associated with incidence of malaria infection including demographic variables, malaria history, reported vector control use, socio economic position, amongst others [17]. Transmission intensity, type of PMC delivery mode, impact of the estimated protective window of SP, and other factors will be adjusted for to assess their impact on the incidence trends [18]. Subgroup analysis will constitute assessing the impact of distance to the health facility as a proxy for access to health services according to the study endpoints highlighted above. Distance will be assessed according to tertials of distance of all study participants to their nearest health facility and as a continuous variable. Alternate model forms including interaction terms as well as semiparametric approaches to account for time-varying intervention effects to account for the expected 4-week prophylactic period of SP will be tested [19]. Because of the challenges in confirming cause of death in those who die in the community and the assumption that severe malaria cases will seek care at a health facility, only the passive cohort data will be used to assess these secondary outcomes [20]. An interim analysis will be conducted after the 4th active cohort visit and the study will be reported according to the ‘Strengthening the reporting of observational studies in epidemiology’ (STROBE) guidelines [21].

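### Interim results are to be shown to clinicians, CHWs and participants while up to half of the active follow-up is still to run, which could shift passive case detection and SP uptake

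*Protocol article*

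**What the plan says.** Only the protocol article is at hand. Four of its statements bear on this point.

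- **Timing.** Data analysis: "An interim analysis will be conducted after the 4th active cohort visit". Active cohort: each child has "seven visits at three-monthly intervals over 18 months, including the initial recruitment visit plus six subsequent follow-up visits".
- **Release.** Dissemination of project findings: at stakeholder meetings in each study country, "the interim and final results will be presented to inform programmatic decision-making on PMC implementation".
- **Audience.** Same section: "Stakeholders will consist of the relevant NMP representative involved in policy", together with "members of the community where the research took place so clinicians, CHWs, and the participants can see how their participation benefited research".
- **Comparison.** Data analysis: the models include "difference-in-difference, and interrupted time-series models comparing intervention and control areas". Malaria incidence counts RDT- or microscopy-confirmed cases found in either cohort. Severe malaria and malaria deaths use passive data only. Children are classified by area of residence, whatever doses they received.

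The article states no limit on what interim content is shown, to whom, or when.

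**The concern.** The audience overlaps with the people who produce the data. Under Overview of PMC intervention, SP is given at health facilities and by CHWs. Under Passive cohort, visits to facilities and CHWs supply the passive cases. Caregivers decide whether a sick child is brought at all, and Aims and objectives concedes that passive detection reaches only those who seek care. The study is open, with one intervention and one control area per country.

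A favourable interim comparison could make caregivers or staff in the intervention area less ready to seek care or test for malaria. That would inflate the apparent effect. It could also raise demand for SP in the control area or prompt a programme change there. Because the primary analysis classifies by residence, added SP in the control area would stay in the comparison and dilute it. An unfavourable result could depress uptake in the intervention area. The direction of bias therefore cannot be fixed in advance. What is exposed is the later part of follow-up, which supplies the late doses and the active cohort's observation after the last dose.

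**Working it through.** **Step 1: timing.** With recruitment as visit 1, visit *n* falls at month 3 × (*n* − 1).
- Visit 7: 3 × 6 = month 18, which reproduces the stated 18 months.
- Visit 4: 3 × 3 = month 9. This leaves 18 − 9 = 9 months (9/18 = 50%) and 3 of 7 visits.

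The 50% is a maximum, counted at the data cut. The article gives no meeting date, and analysis and convening take time. Recruitment continues until the target is reached, so early recruits are past month 9 if the cut waits for the last child's fourth visit.

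**Step 2: what the active cohort has observed by then.** Inputs are the ages at recruitment (Active cohort) and the start of the post-intervention period (Data analysis).

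| | Age at recruitment | Age at visit 4 | Post-intervention starts |
|---|---|---|---|
| Cameroon | 6-9 months | 15-18 months | 24 months |
| Côte d'Ivoire | 10 weeks (about 2.3 months) to 6 months | about 11-15 months | 18 months |

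Counted at each child's own fourth visit, no active-cohort child has reached the post-intervention period. The oldest are 24 − 18 = 6 months short in Cameroon and 18 − 15 = 3 months short in Côte d'Ivoire. If recruitment is staggered by more than that and the cut waits for the last child, a few early recruits would have reached it.

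The passive cohort differs. It enrols children up to 36 months and does not censor by age. Children aged at least 24 − 9 = 15 months (Cameroon) or 18 − 9 = 9 months (Côte d'Ivoire) at baseline reach the post-intervention period by month 9.

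**Step 3: size of the detection bias.** The documents give no figure for this, so the inputs below are assumptions, apart from the planned reductions of 30% and 40% (Sample size).
- Event rates are equal in the two halves of follow-up.
- A share *s* of cases is found through care-seeking, with *s* from 25% to 75%.
- After release, passive detection in the intervention area alone falls by *d* = 10%.

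Apparent RR = true RR × [0.5 + 0.5 × (1 − *s* × *d*)] = true RR × (1 − 0.05 × *s*).

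| *s* | True RR 0.70 becomes | Reads as | True RR 0.60 becomes | Reads as |
|---|---|---|---|---|
| 0.25 | 0.691 | 30.9% | 0.593 | 40.8% |
| 0.50 | 0.683 | 31.8% | 0.585 | 41.5% |
| 0.75 | 0.674 | 32.6% | 0.578 | 42.3% |

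With *d* up to 20% in either direction and the same range of *s*, a true RR of 0.70 lies between 0.65 and 0.75, and one of 0.60 between about 0.56 and 0.65.

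For outcomes drawn from passive data alone, *s* = 1 and the factor at *d* = 10% is 0.95. The article assumes that severe cases will come to a facility, so a 10% drop is probably too large for those.

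**Step 4: SP uptake.** A change in uptake alters true exposure, so it would affect both cohorts, including cases found by household testing. No size is calculated, because the documents give nothing to base it on.

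**The case against.** The strongest reply is that this is an open, ministry-delivered effectiveness study, co-designed with the national programmes, and that giving them interim evidence is a stated purpose. Confidentiality rules from blinded trials do not carry over automatically. This stands: withholding all comparative results from the programmes is a debatable trade-off. It does not justify showing the same results to those who deliver SP and generate the passive cases.

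Four stronger readings are tempting, and the document does not support them.

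- *The plan commits to showing between-area results to participants at exactly half-time.* The article does not say that the interim results are split by area, and it dates no meeting. The phrase "so clinicians, CHWs, and the participants can see how their participation benefited research" looks back and could fit final feedback. However, the audience is defined once, for meetings at which both interim and final results are presented, and results meant to guide PMC decisions are most naturally comparative.
- *All post-intervention observation comes after the release.* This is an active-cohort statement only; see Step 2.
- *A 10% fall in testing turns a true 30% into 33.5%.* That needs every counted case to depend on care-seeking (*s* = 1: 0.70 × 0.95 = 0.665). Active-cohort children are tested at home whether or not they seek care, as the article itself points out.
- *The damage could not be separated afterwards.* PMC receipt is recorded with dates, active visits ask about PMC receipt and where care was sought, and monthly facility attendance is collected to study end. Shifts would be visible in part.

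A condensed article may leave access rules to the full protocol or analysis plan. But the point rests on what the dissemination section affirmatively plans, not on its silence.

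**Conclusion.** The point holds in a limited form. The article plans to present interim results, from an analysis after month 9 of 18, to a group that includes clinicians, CHWs and participants. At most half of the active follow-up is exposed, and less by the time results are shown. Under the assumptions in Step 3, a 10% fall in detection moves an apparent 30% reduction to about 31-33%. That is modest, but systematic and avoidable. A change in SP uptake could act in either area and in either direction, and its size is unknown. The conclusion rests on one inference, that the interim results compare areas; the planned models and the stated purpose of the release make this the natural reading. It is worth correcting before the interim analysis. It does not undermine the study.

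**What to change.** Amend Dissemination of project findings as follows.

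1. Do not show between-area estimates to clinicians, CHWs, participants or communities in the study areas until the last active visit and the passive data cut. Before then, show them only PMC coverage, recruitment and data completeness.
2. If the national programmes need interim comparative results, give them in confidence to the named policy representative.
3. Record the date of that release and any programme change that follows. Plan a sensitivity analysis that separates follow-up before and after that date. Children are older in the later period, so the split should allow for age.

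This takes the scheduled follow-up that site-level groups could influence through knowledge of the comparison from up to 9 of 18 months to none. No sample size, visit or outcome changes. The cost is real but small: site-level feedback on comparative results comes up to about nine months later, and a commitment already made to communities has to be reworded.

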## Discussion

Targeting malaria chemoprevention to those most at-risk of severe malaria has been identified as an important strategy to reduce morbidity and mortality in vulnerable populations. This is the first multi-country, large-scale population observational cohort study that will investigate the effectiveness of programmatically delivered PMC into the second year of life. This research will generate unique and well characterised population cohorts of children followed-up over 18-months in peri-urban and rural African settings. By combining multiple evaluation approaches including both passive and active cohorts, we will be able to address many policy-relevant and implementation questions. Our methodological innovations include use of unique ID numbers per child in both the passive and active cohorts which enables collection and linking of data across multiple health services including EPI vaccination visits, treatment seeking episodes, and any active cohort visits. Similarly, the inclusion of monitoring the older children, beyond the age of PMC eligibility, ensures an internal control as well as monitor the potential impact of PMC on malaria as children age out of the programme [24]. The current study builds on the growing evidence of how chemoprevention strategies can reduce malaria morbidity and mortality when targeted to high-risk populations and can be integrated into routine health services to facilitate rapid scale-up [5]. The participatory approach to research design as well as strong collaborations with national and international policy makers will ensure that the study results are relevant and can be translated widely to inform national policy and practice.

Although PMC is a WHO recommended strategy, there are several gaps in the current evidence that if filled, would help support how, when, and where to implement this strategy to achieve maximum impact. Firstly, the available malaria interventions targeting a reduction in morbidity and mortality, including the recently licensed vaccine, are imperfect and thus only confer partial protection [10, 25]. Therefore, NMPs are faced with having to make decisions on which interventions to invest in, targeted to which populations, where and when. Understanding how the additional doses of SP over the first two years of life impacts malaria burden as well as important nuances including which doses confer more protection and why (e.g., low coverage at a given EPI contact point, administered in the low vs. high malaria transmission season etc.) will provide needed evidence to help justify and optimise PMC implementation [9]. Secondly, controlled trials are essential for generating evidence to inform policy changes and subsequent recommendations for given interventions. However, when such interventions are implemented in a programmatic setting, they are unlikely to achieve the same degree of impact as when done in a controlled setting. Our study will address this specific gap and directly measure the programmatic effectiveness of PMC with SP while the robust study design allowing in depth analysis of key questions including any dose-response effect, which doses maximizes impact, amongst others. This evaluation using real-world data, will therefore, fill important knowledge gaps while simultaneously supporting broader analysis on cost-effectiveness of the intervention or the implications of parasite drug-resistance profiles on the protective effectiveness of SP.

In conclusion, our research team will undertake a comprehensive and robust evaluation of the effectiveness of PMC to reduce malaria burden. Global trends in malaria have had recent trends in reducing burden stagnating or in some cases, increasing. Therefore, new evidence-based strategies are urgently needed to expand the arsenal of malaria control tools available. The participatory and inclusive nature of the study design and broader research collaboration ensures the potential for the findings to be widely implemented by other NMPs wanting to expand their arsenal of options available to help reveres these trends.

## Data Availability

No datasets were generated or analysed during the current study.

## Abbreviations

CHW: Community Health Worker
CI: Confidence Interval
eCRF: Electronic Case Record Form
EPI: Essential Programme of Immunization
Hb: Haemoglobin
IPTi: Intermittent Preventative Treatment for malaria in Infants
ITT: Intention to Treat
NMP: National Malaria Programme
MoH: Ministry of Health
ODK: Open Data Kit
PMC: Perennial Malaria Chemoprevention
RDT: Rapid Diagnostic Test
SP: Sulfadoxine-Pyrimethamine
WHO: World Health Organization
